## Methods/Design

### Study design

Institutional review board approval was granted for this study through the University of British Columbia Clinical Research Ethics Board (H07-02330). Health Canada Clinical Trial Application Notice of Authorization was obtained on 10 May 2013 (company code 31784, file number 187476). This trial is registered with ClinicalTrials.gov (NCT00799214). This study conforms to CONSORT 2010 guidelines for randomized control trials.

Based on preliminary data, the success rate for the boric acid treatment group is predicted to be approximately 77–88 % [25, 32] in treating BV. Metronidazole would be expected to be 70–80 % [11, 12, 15–18] effective in treating BV, as compared with a 30 % success rate of a placebo group [11, 12]. The Nugent score is found to be >95 % sensitive [33] for detecting BV. We chose a non-inferiority limit of 10 %, as this will allow for a clinically relevant difference between the metronidazole treatment group and the boric acid group. Also, this is approximately 25 % of the expected difference between results obtained for the metronidazole standard treatment group and the placebo group. Accounting for a non-inferiority limit (delta) of 10 %, testing for a significance level of 0.05 and power of 80 %, we require approximately 63 subjects per group. To allow for a dropout rate of 25 %, we set a target rate of 80 subjects per treatment arm. If there is a true difference in favor of the experimental treatment of 8 %, then 126 patients (total for two groups of 63) are needed, to be 80 % sure of the upper limit of a one-sided 95 % confidence interval, using a binary outcome, non-inferiority trial power calculator [34].

We felt it important to include a placebo treatment arm in this study for different reasons: (1) this is the first randomized controlled trial to use intravaginal H_3_BO_3_; thus, comparing it to placebo for safety and effectiveness would be of clinical interest (that is, perhaps it is not comparable to metronidazole in effectiveness but it is still significantly better than placebo), (2) having a placebo group in a non-inferiority trial acts as a sensitivity assay and internal validator for this type of trial [35], (3) comparing metronidazole effectiveness and safety with results obtained for a placebo group in 16–19-year-olds has not previously been done and would also be of clinical interest.

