### Statistical considerations

The primary outcome measure is a non-inferiority per-protocol comparison of effectiveness of H_3_BO_3_ with metronidazole at day 17, as measured by Nugent score, in 16–50-year-olds with a *z*-based confidence interval for the difference of two proportions. This was chosen as the primary outcome measure because the immediate effect of H_3_BO_3_ after a 10-day treatment compared with metronidazole was our most important question about BV treatment. A change from a baseline Nugent score ≥7 to a Nugent score <7 is considered a cure of BV. Treatment failure will be reported as a positive Nugent score ≥7 at day 17.

Secondary outcome measures include a non-inferiority intention-to-treat comparison of effectiveness of H_3_BO_3_ with metronidazole at day 17, as measured by Nugent score in 16–50-year-olds, with a *z*-based confidence interval for the difference of two proportions. We will use this comparison to confirm the robustness of our per-protocol comparison but the per-protocol analysis will be the primary determinant of the non-inferiority test. In addition, we will conduct a non-inferiority comparison of effectiveness of H_3_BO_3_ and metronidazole at day 40, as measured by Nugent score in 16–50-year-olds analyzed on both per-protocol and intention-to treat principles, with a *z*-based confidence interval for the difference of two proportions, and safety consideration including intolerable adverse effects requiring patient discontinuation of the 10-day treatment. To control for multiple testing, we will use a Bonferroni-type correction. To account for both intention-to-treat and per-protocol analyses, and two timepoint analyses, the threshold for statistical significance will be set at 0.01 (approximately 0.05 divided by 4).

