The following are tertiary outcome measures and no formal sample size calculations were made. Minor adverse effects (side effects not causing the patient to discontinue treatment) will be reported and compared between the treatment arms but will not be considered as treatment failure. We will examine the adolescent population, the 16–19 year old subgroup, for non-inferiority for effectiveness of H_3_BO_3_, as compared with metronidazole, at the end of the study. Finally, we will test for superiority of the effectiveness and safety of H_3_BO_3_ compared with placebo in both the 16–50-year-olds and in the 16–19 year old subgroup. In addition, our study is the first to be able to examine 16–19-year-olds for the effectiveness and safety of metronidazole compared with placebo.

95 % confidence intervals will be established. Missing data (participants who fail to complete follow-up for any reason) are accounted for by an anticipated 25 % lost-to-follow-up rate. Data will be blindly collected by the outcome assessors from the participating clinics and entered into an electronic database. The study pharmacist will provide the randomization code for the data to a third-party statistician and the data will be analyzed. Self-reported participant satisfaction criteria included at the end of the daily treatment diary will use a five-point rating scale to record: effectiveness in curing BV symptoms, side effects, ease of use, likelihood they would use it again for BV treatment, likelihood they would recommend it to someone else for BV treatment.

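### The placebo arm is justified as the assay-sensitivity check, yet the listed analyses compare metronidazole with placebo only in 16–19-year-olds, and the non-inferiority decision depends on no placebo result

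*Protocol article*

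**What the plan says.** Under Study design, the protocol article gives three reasons for a placebo arm. The second is that "having a placebo group in a non-inferiority trial acts as a sensitivity assay and internal validator for this type of trial". The third concerns adolescents: "comparing metronidazole effectiveness and safety with results obtained for a placebo group in 16–19-year-olds has not previously been done". The same section sets the margin at 10 percentage points and supports it partly by noting that "this is approximately 25 % of the expected difference between results obtained for the metronidazole standard treatment group and the placebo group". The expected cure rates are 70–80 % for metronidazole and 30 % for placebo.

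Under Statistical considerations, the primary analysis is boric acid against metronidazole at day 17 in 16–50-year-olds, and "the per-protocol analysis will be the primary determinant of the non-inferiority test". The secondary analyses repeat that two-arm comparison by intention to treat and at day 40.

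Placebo enters the effectiveness analyses only in the tertiary list, which opens with "The following are tertiary outcome measures and no formal sample size calculations were made". Two placebo comparisons follow:

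- Boric acid, in all ages and in adolescents: "we will test for superiority of the effectiveness and safety of H_3_BO_3_ compared with placebo in both the 16–50-year-olds and in the 16–19 year old".
- Metronidazole, in adolescents: "our study is the first to be able to examine 16–19-year-olds for the effectiveness and safety of metronidazole compared with placebo".

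**The concern.** A non-inferiority result means something only if the control worked in the trial at hand. A placebo arm lets the trial show this directly, provided that the control is compared with placebo in the population and at the time of the primary test (here 16–50 years, day 17). The article claims this benefit for its placebo arm, which takes one third of participants. Its list of analyses then names the full age range for boric acid against placebo, but only adolescents for metronidazole against placebo. No placebo result enters the decision on non-inferiority.

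Two things are at stake. Non-inferiority could be declared against a control that had not been shown to work in these participants. The margin also rests on the size of the metronidazole effect, and no listed analysis checks that effect in the main population.

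**Working it through.** **Inputs from the article (Study design).** Margin 10 points; metronidazole 70–80 %; placebo 30 %; true advantage of boric acid 8 points; one-sided 95 % interval; power 80 %; 63 per group; 80 per arm with 25 % dropout, so 80 × 0.75 = 60 evaluable.

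**1. The plan's own sample size.** Assume 75 % for metronidazole, the midpoint of the stated range, and 83 % for boric acid.

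n = (z₀.₉₅ + z₀.₈₀)² × [p₁(1−p₁) + p₂(1−p₂)] / (0.08 + 0.10)²
= (1.645 + 0.842)² × (0.1875 + 0.1411) / 0.0324 ≈ 62.7, rounded up to 63.

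This reproduces the stated 63. At one-sided 0.025 the same inputs give 80, so the stated figure belongs to one-sided 0.05.

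**2. The margin.** 10/(70−30) = 25 % and 10/(80−30) = 20 %. The stated quarter agrees with the expected rates, but it depends on metronidazole achieving them.

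**3. The two-arm rule if neither drug beats placebo.** Set boric acid and metronidazole both at 30 %, with 63 per group. Non-inferiority is declared when the lower limit of the z-interval for boric acid minus metronidazole lies above −10 points.

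SE = √(2 × 0.30 × 0.70 / 63) = 0.0816, and 0.10 / 0.0816 = 1.225.

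At one-sided 0.05 the chance is Φ(1.225 − 1.645) = Φ(−0.420) ≈ 34 %. Exact binomial enumeration with the unpooled interval gives:

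| One-sided level | Chance of declaring non-inferiority |
|---|---|
| 0.05 | 34 % |
| 0.025 | 24 % |
| 0.01 | 14 % |

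With 60 per group the figures are 33 %, 23 % and 14 %.

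**4. Power of the check in all 16–50-year-olds.** 60 per arm, placebo 30 %, two-sided z-test with pooled variance under the null:

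power = Φ{[d − z√(2p̄(1−p̄)/n)] / √[(p₁(1−p₁) + p₂(1−p₂))/n]}

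For 70 % against 30 % at 0.05: (0.40 − 1.96 × 0.0913) / 0.0837 = 2.64, which gives 99.6 %.

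| Metronidazole cure | Two-sided 0.05 | Two-sided 0.01 |
|---|---|---|
| 70 % | 99.6 % | 97.6 % |
| 75 % | >99.9 % | 99.6 % |
| 80 % | >99.9 % | >99.9 % |
| 60 % (assumption, below the stated range) | 92.0 % | 77.7 % |

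For 90 % power at two-sided 0.05, 31, 24 or 19 per arm suffice at 70, 75 or 80 % cure. Further per-protocol exclusions are therefore affordable.

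**5. Cost to the primary claim.** Requiring the check as well can lower the power for non-inferiority by no more than the check's own failure rate. At 70 % cure and two-sided 0.05 that is 100 − 99.6 = 0.4 points.

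**6. The adolescent comparison as a substitute.** The article does not give the subgroup's size. Assuming 16–19-year-olds are 10 % or 20 % of 60 evaluable per arm (6 or 12), power at 75 % against 30 %, two-sided 0.05, is about 33 % or 61 %. The normal approximation is rough at these sizes.

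**The case against.** Three arguments carry weight.

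**The list may be incomplete.** This is a condensed article, and the adolescent sentence reads as a statement of novelty that echoes the third reason for the placebo arm. It does not say that metronidazole will be compared with placebo nowhere else. Day-17 swabs are taken in every arm, and confidence intervals are promised. A reader might infer that the trial will never estimate the metronidazole–placebo difference in adults. The article does not support that. It does, however, go beyond silence: it names populations for each placebo comparison, gives metronidazole the narrower one, and states what decides non-inferiority without reference to placebo.

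**Boric acid against placebo in 16–50-year-olds gives some protection.** If both drugs performed like placebo, this test would usually fail and expose the problem. If it succeeded, the trial would have shown that it can separate an active treatment from placebo. A reader might infer that a non-inferiority claim against a failed control would go unnoticed; that is too strong. But the comparison is tertiary, does not condition the claim, and does not show that metronidazole had the effect on which the margin rests.

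**Metronidazole is presented as an established treatment.** Nothing in the article suggests that it will underperform here, and nothing supports reading its dose as weak. The 30 % scenario shows what the rule allows and is not a forecast. Still, the article itself chose to offer placebo as an internal validator, without relying on the earlier trials alone.

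A formal gate is also not the only possible remedy. A pre-stated estimate with its interval would be a weaker alternative.

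**Conclusion.** The point holds in a limited form. The article's stated purpose for the placebo arm and its margin rationale both rest on metronidazole against placebo in the main population. Its listed effectiveness analyses give that comparison only for 16–19-year-olds, as a tertiary item, and no placebo result conditions the non-inferiority decision.

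If boric acid and metronidazole both cured 30 %, the two-arm rule would declare non-inferiority in about a third of trials at the one-sided 0.05 used for sizing, and in about one in seven at one-sided 0.01. These figures assume 63 per group and an unpooled z-interval. They do not mean that a third of such claims would pass unchallenged, because the tertiary boric acid comparison would usually give warning.

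The missing check is almost certain to succeed if the stated cure rates are right, so the change should be made.

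**What to change.** Before unblinding, pre-specify metronidazole against placebo in all 16–50-year-olds, on day-17 Nugent cure. Use the same per-protocol set as the primary analysis, with intention to treat as support. Report the difference and its confidence interval, so that the margin can be judged against the effect actually observed. State that non-inferiority will be interpreted only if metronidazole is superior to placebo.

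State the significance level of the check. Because the claim then requires both results, the check takes no alpha from the primary test and need not share the article's 0.01 multiplicity threshold, though power is adequate at that level too under the stated rates.

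The cost is one comparison on data already collected and a sentence in the protocol and analysis plan. The article reports recruitment as open, and the pharmacist releases the randomization code to the statistician for the analysis, so the sentence can be added while the study is blinded.

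The downside is that non-inferiority cannot be claimed if the check fails. At two-sided 0.05 with 60 per arm, that would be about 8 % of trials if metronidazole cured only 60 % (an assumption), and at most 0.4 % at the stated 70–80 %.

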### Safety assessments

Emergency telephone contact with the investigators will be available for any questions or problems related to the treatment. On day 5 of the treatment, the participant will receive a call, text, or email from one of the investigators to determine and record compliance, side effects, BV symptoms, and satisfaction with treatment. The study pharmacist will be informed by the recruiting clinician of the participant’s full name, date of birth, and personal health number, and the study number assigned, so that the study pharmacist can enter the medication name into the British Columbia PharmaNet Database (the provincial pharmacy database). This safety measure ensures that subsequent treating physicians throughout the province will have access to details of the treatment received, in case of a safety concern and a need to unblind the participant’s medication should the participant present with an emergency. Non-emergency access to the provincial pharmacy database is not allowed, to protect the participant’s identification of the blinded treatment.

If at any time the participant reports intolerable side effects (vaginal discomfort, intolerable vaginal discharge, urticaria, or secondary yeast infection) during treatment, or exacerbation of symptoms at any point, she may voluntarily discontinue the treatment and leave the study without prejudice, and her doctor or another physician may provide treatment as per usual standard of care.

As neither metronidazole nor H_3_BO_3_ treatments provided to patients are in amounts considered toxic when taken intravaginally or if accidentally ingested, should there be any occurrence of serious adverse effects (neurological, cardiac, respiratory, gastrointestinal, or anaphylactic reactions) during any of the treatments, the study will be put on hold until an investigation can be held. In the case of serious adverse effects found to be caused by the treatment, the study will be stopped, and the study unblinded and decoded by the study pharmacist. The investigators, participants, and clinicians involved in the study would be informed for the reason for stopping the study.

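### The 25% enrolment allowance is presented as the handling of missing data, but it gives no outcome to women without a swab, so the intention-to-treat comparison as described cannot test robustness to missing outcomes

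*Protocol article*

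**What the plan says.** The Statistical considerations section defines missing data broadly, as any failure to complete follow-up, and gives one sentence on how it is dealt with: "Missing data (participants who fail to complete follow-up for any reason) are accounted for by an anticipated" 25% loss rate. The Study design section shows where that rate is used: about 63 women per group are required, and the target becomes 80 per arm to allow for 25% dropout.

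Four other statements bear on the point.

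- **Outcome definition (Statistical considerations).** Cure is a move from a baseline Nugent score of 7 or more to a score below 7. Failure is a score of 7 or more at day 17. Both need a swab result.
- **Leaving the study (Safety assessments).** A woman with intolerable side effects during treatment, or with worsening symptoms at any time, is told that "she may voluntarily discontinue the treatment and leave the study without prejudice", and may then be treated by her own or another physician.
- **Stopping for side effects (Outcomes and assessment).** This counts as treatment failure for the safety outcome. Nothing is said of its effect on the effectiveness outcome.
- **Role of intention-to-treat (Statistical considerations).** Per-protocol decides the non-inferiority test. Of the day-17 intention-to-treat comparison the article says: "We will use this comparison to confirm the robustness of our per-protocol comparison".

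**The concern.** Enrolling more women and analysing missing outcomes are different things. The first restores the number of observed results. It does nothing about bias if the women who are lost differ from those who return, or if the two arms lose different kinds of women.

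Here there is a stated route for such loss: women who tolerate treatment badly or get worse may leave. If they give no swab, the outcome definitions make them neither cured nor failed. The per-protocol set would omit them and so, on the natural reading, would the intention-to-treat set. The analysis meant to confirm robustness would then share the primary analysis's exposure to informative loss. In a non-inferiority trial this matters, because an arm that loses its unsuccessful cases can look as good as the comparator.

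**Working it through.** **1. The article's own figure.** Inputs from Study design: margin 10 points ("We chose a non-inferiority limit of 10"%), "testing for a significance level of 0.05 and power of" 80%, a one-sided 95% interval, and a true advantage of 8 points for boric acid. Metronidazole is put at 70–80%; the value entered is not stated, so I take the midpoint, 75%, against 83%.

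n = (z₀.₉₅ + z₀.₈₀)² × [p₁(1−p₁) + p₂(1−p₂)] / (margin + difference)²

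= 2.486² × [0.75×0.25 + 0.83×0.17] / 0.18² = 62.7, so 63. The figure reproduces.

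**2. What the 25% does.** 63 × 1.25 = 79, close to the stated 80. It is a sample-size step and nothing more. With 25% lost, 80 × 0.75 = 60 women per arm have an outcome and 20 do not. (Dividing instead, 63/0.75 = 84. The shortfall is a side issue: power is about 78% with 60 per arm and 80% with 63.)

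**3. Can losses of this size change the conclusion?** The documents give no loss or cure rates by arm for women who leave, so all counts below are assumed. Differences are boric acid minus metronidazole. Lower limit = difference − 1.645 × √[p₁(1−p₁)/n₁ + p₂(1−p₂)/n₂], one-sided 95%, z-based and unpooled.

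*Unequal loss.* 80 per arm, with 16 metronidazole women (20%) and 24 boric acid women (30%) missing: 40 of 160, or 25% overall.

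| Analysis | Metronidazole | Boric acid | Difference | Lower limit |
|---|---|---|---|---|
| Observed swabs only | 48/64 = 75.0% | 47/56 = 83.9% | +8.9 | −3.1 |
| Missing counted as failures | 48/80 = 60.0% | 47/80 = 58.8% | −1.3 | −14.0 |
| About 30% of missing cured (5 of 16; 7 of 24) | 53/80 = 66.3% | 54/80 = 67.5% | +1.3 | −11.0 |

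The third row uses the article's 30% resolution rate without treatment. The first row meets the 10-point margin; the other two do not.

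*Equal loss.* 20 missing per arm; observed cures 45/60 metronidazole and 50/60 boric acid.

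- Observed swabs only: +8.3, lower limit −3.8.
- Missing counted as failures, 45/80 v 50/80: +6.3, lower limit −6.5. Non-inferiority still holds.
- Tipping point, with 15 of 20 missing metronidazole women cured (60/80): if 11 of 20 missing boric acid women are cured (61/80) the lower limit is −9.9; if 10 are (60/80) it is −11.3.
- Extreme case against boric acid, 65/80 v 50/80: −18.8, lower limit −30.2.

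The equal-loss case also shows why counting every missing woman as a failure is not a sufficient check: it left the conclusion intact, whereas the tipping-point analysis found a plausible region where it fails.

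**The case against.** The strongest reply is that this is a condensed article. Analysis-set definitions and imputation rules commonly sit in the full protocol or analysis plan, and the sentence may simply point back to the sample-size section. That would be a good answer had the article been silent. It is not silent: it says that missing data are accounted for, and names a mechanism that cannot do so. The statement is wrong as it stands.

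Several limits on the concern do hold.

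- **Exclusion is not stated.** A reader might infer that the article drops women without a swab from intention-to-treat. No section says so. It is the natural consequence of the missing-data sentence taken with the outcome definitions.
- **Leaving is optional.** A woman may stop treatment and still return, and she is then scored by Nugent like anyone else. Attaching side-effect stopping to the safety outcome does not remove her from effectiveness. That a poorly tolerated arm sheds its failures is a possibility, not something the text fixes.
- **Intention-to-treat is not worthless.** A reader might infer that it nearly equals the per-protocol set and cannot confirm it at all. The eligibility table lists many conduct conditions (intercourse, intravaginal products, alcohol, new medication). Women who break them but return could be added. The weakness concerns missing outcomes only.
- **Simple point-estimate examples overstate the case.** Suppose completers are cured 75% in both arms and 20% of boric acid against 5% of metronidazole women leave uncured. The all-randomised difference is 0.75×0.80 − 0.75×0.95 = −11.3 points. But completers at 48/64 and 57/76 already have a lower limit of −12.1, so the missing women change no conclusion there. If 30% of leavers resolve, the difference is (0.60 + 0.06) − (0.7125 + 0.015) = −6.75.

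**Conclusion.** The concern holds in a bounded form. The article states a way of handling missing outcomes that protects precision only. On the natural reading, about a quarter of women contribute to neither effectiveness comparison, and the stated exit route makes it plausible that their loss is related to outcome. The intention-to-treat comparison then cannot serve as a check on missing outcomes, though it keeps some value for non-adherence.

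As to size, loss at the anticipated overall rate can reverse the result: in the unequal-loss example the lower limit moves from −3.1 to −14.0. This rests on assumed counts, unequal loss and missing counted as failures; the reversal persists if about 30% of the missing are cured. It shows what could happen, not what to expect. With equal loss and all missing counted as failures, the conclusion did not change.

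This should be fixed. It stops short of a fatal flaw because per-protocol is the declared primary analysis, the exclusion is inferred, and a fuller analysis plan may exist.

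**What to change.** 1. Delete the claim that the 25% allowance accounts for missing data. Describe it only as a sample-size allowance.
2. Tell sites to seek the already planned day-17 and day-40 swabs from women who stop treatment, unless they withdraw consent. Separate stopping treatment from leaving follow-up in the wording.
3. Define the intention-to-treat set as all randomised women with a baseline Nugent score of 7 or more, analysed as allocated. Pre-specify the method for a missing score, for example multiple imputation.
4. Add a tipping-point analysis that worsens only the boric acid arm, because imputing failure equally in both arms can pull them together.

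Scoring women who leave for side effects as not cured changes what is being estimated, since cure is defined by Nugent score alone. It may be a sensitivity analysis but is not required as a correction.

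The cost is a revised paragraph, a follow-up instruction to sites and a little more analysis. The intention-to-treat result may be less favourable to boric acid. The article reports recruitment as open, so the swab instruction is the urgent part: swabs not taken cannot be recovered. The analysis rules should be fixed before the randomisation code is released to the statistician.

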### Participants and eligibility

Women who present to their clinician at participating family practice clinics with symptoms of BV are offered an opportunity to participate in the study. Participants are given the informed consent form explaining the three possible treatment arms, and that participation will include three visits (the initial visit, day 0; day 17–19 [7–9 days after the treatment end to measure the primary endpoint]; and day 40–42 [30–32 days after the treatment end as a secondary endpoint]) involving three examinations, including a pregnancy test. There are no visits to the clinic while the participants are administering the 10-day treatment unless there are any concerns. Women are included in the study if they are symptomatic for BV, meet three of four Amsel criteria on the initial day of the study and subsequently have a swab graded with a Nugent score ≥7. Detailed eligibility criteria are listed in Table 1. In general, participants cannot be pregnant, menopausal, have another vaginal infection, or have an intrauterine device. Written consent is obtained prior to treatment intervention. Women who choose to participate receive their medication for free. There is a draw for recruited women to win a small gift certificate.

**Table 1 Tab1:** Eligibility criteria

Inclusion criteria	Exclusion criteria
Must be 16–50 years old and pre-menopausal. Capable of giving written informed consent.	Younger than 16 or post-menopausal.
Fluent spoken and written English.	Menstruating at diagnosis.
Agrees to examination on enrollment day, day 17–19 and day 40–42.	Symptoms so severe as to make allocation to placebo unacceptable to the woman.
Has a negative pregnancy test during the study. Agrees to follow study protocol and is reliable for follow-up.	Currently pregnant or at high risk for pregnancy.
Has documented bacterial vaginosis infection by positive vaginal swab (minimum Nugent score of ≥7) and meets three of four Amsel criteria.	Current active sexually transmitted infection (chlamydia, gonorrhea, trichomonas).
Agrees to refrain from vaginal intercourse for the 10 days of treatment (or to use non-lubricated non-latex condoms if unavoidable). Agrees not to douche or use any intravaginal products during treatment (including tampons, medications, devices).	Current yeast infection as determined by history, physical examination, and swab analysis.

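### The 25% allowance is described as loss to follow-up, but the deciding analysis is per-protocol: no stated allowance covers attenders who are excluded, and 80 per arm less 25% leaves 60, not 63

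*Protocol article*

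**What the plan says.** Three statements in the protocol article bear on this point.

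- **Required number (Study design).** The size of each arm before any allowance is given as follows: "Accounting for a non-inferiority limit (delta) of 10 %, testing for a significance level of 0.05 and power of 80 %, we require approximately 63". The same paragraph gives the assumed effect, "If there is a true difference in favor of the experimental treatment of 8 %, then 126 patients (total for two groups of 63) are needed", and the sidedness, "to be 80 % sure of the upper limit of a one-sided 95 % confidence interval".
- **Allowance (Study design and Statistical considerations).** Study design says: "To allow for a dropout rate of 25 %, we set a target rate of 80 subjects per treatment arm". The later section describes the same percentage as "Missing data (participants who fail to complete follow-up for any reason) are accounted for by an anticipated 25 % lost-to-follow-up rate".
- **Deciding analysis (Statistical considerations).** "The primary outcome measure is a non-inferiority per-protocol comparison of effectiveness of H_3_BO_3_ with metronidazole at day 17", and "the per-protocol analysis will be the primary determinant of the non-inferiority test". The intention-to-treat comparison is there to confirm robustness.

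The article also sets conduct conditions that a woman could breach and still give a day-17 swab. One is in Table 1: "Agrees to refrain from vaginal intercourse for the 10 days of treatment" (or use of the study condoms if unavoidable). Others are no alcohol, no intravaginal products and no new medicines during treatment. The regimen is ten evenings of self-applied cream, recorded in a diary, and each follow-up visit has a three-day window.

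**The concern.** A woman can leave a per-protocol set in two ways: she does not return, or she returns but did not follow the protocol closely enough to count. The allowance is described only in terms of the first. The phrase about any reason widens the reasons for not completing follow-up, but it does not bring in women who do complete it.

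What is at stake is the number of women in the comparison that decides the trial. The 63 per group must be reached in the day-17 per-protocol set. If exclusions come on top of the stated loss, fewer than the planned number arrive there. The confidence interval widens, and a boric acid arm that really performs as assumed is more likely to miss the 10-point margin. The article itself states the required number, the allowance, what the allowance covers and the deciding set, so the mismatch can be seen without any further document.

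**Working it through.** **Inputs from the article:** margin 10 points; one-sided 0.05; power 80%; true advantage of 8 points for boric acid; 63 per group; 80 per arm; 25% allowance.

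**Assumed inputs:** metronidazole cure 75%, the midpoint of the stated 70–80%, and hence 83% for boric acid. The article does not give the point value it used. It gives no per-protocol exclusion rate either, so 5–20% of attenders is an assumed range.

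**Step 1: reproduce the 63.** With unpooled variances,

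n = [0.75 × 0.25 + 0.83 × 0.17] × (1.645 + 0.842)² / (0.08 + 0.10)² = 0.3286 × 6.185 / 0.0324 = 62.7, so 63.

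This matches the article. The match depends on the 75%: a control rate of 70% would give 73 and 80% would give 51.

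**Step 2: apply the allowance.** 80 × (1 − 0.25) = 60 per arm, 3 short of 63. Keeping 63 after a 25% loss needs 63 / 0.75 = 84. The 80 is close to 63 × 1.25 = 78.75, which adds 25% to the required number instead of dividing by 0.75.

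**Step 3: power at a given evaluable number.** Power = Φ(0.18 / SE − 1.645), with SE = √(0.3286 / n).

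- n = 63: SE = 0.0722, power 80.2%.
- n = 60: SE = 0.0740, power 78.4%.

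**Step 4: attrition that 80 per arm can bear.** 1 − 63/80 = 17/80 = 21.25%. Loss by day 17 and per-protocol exclusions together must not exceed this. A 25% loss by day 17 already does, with no exclusions at all.

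**Step 5: exclusions added to the full 25% loss.**

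| Attenders excluded (assumed) | Evaluable per arm | Power |
|---|---|---|
| 0% | 60 | 78.4% |
| 5% | 57 | 76.6% |
| 10% | 54 | 74.6% |
| 15% | 51 | 72.5% |
| 20% | 48 | 70.2% |

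**Step 6: the favourable case.** The 25% refers to completing follow-up, which runs to day 40–42. Suppose only 12% are lost by day 17 and 10% of attenders are excluded (both rates assumed). Then 80 × 0.88 × 0.90 = 63.4, and the stated 80% holds.

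**The case against.** A reader might infer that the stated 80% is simply not the power of the primary analysis. The article does not support that. The 80% belongs to 63 evaluable women per group, and it is the power of the per-protocol test whenever 63 reach that set. Nothing in Study design ties it to an analysis of all completers.

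A reader might also take the 25% as strictly separate from protocol deviation, so that a full second layer of attrition must be added. That goes too far for three reasons:

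- Study design uses the general word dropout.
- Under Safety assessments, women with intolerable side effects may stop treatment and leave the study. Those early stoppers are an obvious per-protocol loss and already sit inside the 25%, so a separate layer risks counting some women twice.
- Women lost only between day 17–19 and day 40–42 still contribute to the primary comparison.

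It can further be said that the Table 1 conditions are mostly agreements at enrolment. The article does not say which breaches remove a woman from the per-protocol set, and a condensed article may leave that definition to the full protocol or analysis plan. This is fair, and the missing definition is not raised here. Finally, both 240 in total and 80 per arm are given as minimums, which permits further recruitment but commits to none.

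These arguments remove any claim that power is certainly 70–77%. They leave two things standing: the allowance is described in terms that do not match the deciding set, and 25% off 80 leaves 60 even before any exclusion.

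**Conclusion.** The point holds as a mismatch between the allowance and the deciding analysis. No stated allowance covers women who attend day 17–19 and are excluded for deviations. On the article's own 80 and 25%, at most 60 per arm remain against the 63 required. That is about 78% power instead of 80%, a loss of under 2 points, and it comes from the inflation step alone.

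Any further fall depends on rates that the article does not give. It is about 77–70% if the whole 25% is lost by day 17 and 5–20% of attenders are then excluded. It is nil if total day-17 non-evaluability stays at or below 21.25%.

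All power figures assume 75% v 83% cure, a 10-point margin, one-sided 0.05 and the unpooled normal approximation. They do not address the separate question of the 0.01 significance threshold under Statistical considerations. The matter merits correction because a stated figure on which the trial relies should refer to the set that decides it.

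**What to change.** - **Study design:** define the allowance as total non-evaluability for the day-17 per-protocol set, that is, loss by day 17 plus per-protocol exclusions. Restate the evaluable number per arm and the power it gives. If 25% is to cover both, that is 60 per arm and about 78% under the assumptions above, with the assumed cure rates stated.
- **Statistical considerations:** align the sentence on missing data, so that the 25% has one meaning throughout.
- **Conduct:** while recruitment is open, monitor the pooled, blinded count of per-protocol-evaluable women against the restated number. At 60 per arm this is 3 × 60 = 180 of 240. A pooled count cannot show an imbalance between arms, so it is a warning signal and not proof that each arm has reached its number.

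The cost is a wording change, one recalculation and a slightly less favourable stated power. The correction itself requires no extra participants. If the trial team preferred to keep 63 evaluable per arm with 25% total non-evaluability, the target would be 84 per arm, or 252 in three arms.
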